#### Secondary efficacy outcomes

Intention-to-treat analysis shall be followed for analysis of secondary outcomes. For count secondary outcomes, all sick visits, malaria-specific sick visits, all-cause hospitalisations, malaria-specific hospitalisations, serious cardiac adverse events and SCA-related vaso-occlusive events, we shall fit Poisson regression models and compare events between the intervention groups using incidence rate ratios. Negative-binomial regression models will be fitted if there is overdispersion. Model adjusters shall be informed by imbalances in baseline characteristics between the intervention groups. We shall fit a binary logistic model to compare the odds of death between the two intervention groups. Death shall likely be a rare outcome in this study, and often, binary logistic regression models face convergence problems due to the sparse outcome. We shall instead fit models using the firth method, which avoids the convergence challenges of the logistic regression model when the outcome is rare. We shall report odds ratios as measures of association. We shall also test if the change in QTc length from baseline is > 60 ms using a one-sided *t*-test. We will provide a list of individual participant changes in QTc length from baseline. Exploratory quantitative outcomes shall be summarised by the intervention arm using descriptive statistics. Qualitative exploratory outcomes such as user and provider experiences of the intervention, satisfaction with the intervention and treatment preference will be described as text. We shall also present a list of adverse events and document if they were related to the study drug or not.

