Artemisinin-containing combination therapies (ACTs) such as DP are now the standard for the treatment of *Plasmodium falciparum* malaria in both children and adults [6]. A systematic review of the efficacy and safety of ACTs showed that DP is very effective and provides a long duration of post-treatment prophylaxis similar to mefloquine and a longer duration than amodiaquine or lumefantrine-based combinations [6, 7]. Because of its long half-life, piperaquine has great potential for use as the ACT of choice for intermittent treatment and chemoprophylaxis, as was shown in intermittent preventive treatment (IPT) studies in children [8]. We propose dihydroartemisinin-piperaquine as the chemopreventive agent of choice for children with SCA on the continent.

A trial with monthly DP used as IPT in Thai adults showed it to be well-tolerated, safe and highly effective [9]. The most important determinant of protective efficacy was the trough plasma concentration of piperaquine, and this was determined by the dosing frequency. The study suggested that for effective prevention of malaria, DP should at least be given monthly to achieve steady-state concentrations above the minimum inhibitory concentrations and sustained prophylactic levels. Piperaquine is currently only available in the fixed-dose combination with dihydroartemisinin (DHA) as DP. The DHA component, eliminated within a few hours, is not expected to contribute significantly to chemoprevention effects, yet may provide a degree of protection against the development of piperaquine resistance in the population.

Side effects of DP in adults include transient drops in haemoglobin by day 7 (seen with all ACT), headache, weakness, and fever. Its main safety concerns relate to its dose-dependent QT prolongation seen in clinical trials, including our post-discharge chemoprevention of malaria in transfused children (PMC) study [10]. Nevertheless, the side effects of DP are mild and similar to that seen with other anti-malarial drugs [11]. There is also no indication from the data signalling that it is associated with clinically significant arrhythmia [12].

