### Sample size {14}

The minimum incidence rate of clinical malaria in SCA patients receiving monthly SP is estimated at 0.2 events per year. Assuming an effect size of 50% if DP is used (i.e. a 50% reduction in the rate as in Bigira et al. [27] that is, a hypothesised incidence rate of 0.1 events per person per year in the DP group), at a power of 0.9 and 0.05 level of significance, we will need 438 individuals to be followed up for 18 months. Allowing for 20% losses to follow-up, we shall need 548 participants (274 in each group) to be followed for an average of 18 months, equivalent to 9864 person months, or 824 participants for an average follow-up of 12 months, equivalent to 9888 person-months.

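### Serious cardiac adverse events are given ordinary Poisson regression with no rule for an empty arm, although the same paragraph adopts a sparse-data method for death

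*Protocol article*

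**What the plan says.** The statistical section on secondary outcomes lists serious cardiac adverse events together with sick visits, hospital admissions and vaso-occlusive events, and assigns one model to them all: "serious cardiac adverse events and SCA-related vaso-occlusive events, we shall fit Poisson regression models". Arms are to be compared by incidence rate ratios. Covariates are to be picked according to which baseline characteristics turn out unbalanced. One fallback is stated: "Negative-binomial regression models will be fitted if there is overdispersion".

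The paragraph then turns to mortality: "Death shall likely be a rare outcome in this study, and often, binary logistic regression models face convergence problems due to the sparse outcome". The remedy follows: "We shall instead fit models using the firth method, which avoids the convergence challenges of the logistic regression model when the outcome is rare". It is attached to death alone.

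The Safety outcomes list defines a serious cardiac event as a convulsion or syncope in the 48 hours following a dose. On cardiac risk with DP, the background says "Its main safety concerns relate to its dose-dependent QT prolongation seen in clinical trials" and adds "There is also no indication from the data signalling that it is associated with clinically significant arrhythmia". Cardiac safety under cumulative dosing is also a named secondary objective. No expected rate of cardiac events appears anywhere in the article.

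**The concern.** The plan acknowledges that sparse outcomes break ordinary regression and acts on this for one outcome. In the same paragraph it commits another outcome, which may be equally sparse, to a model that has no finite rate ratio when one arm has no events. A negative-binomial model does not help, because it addresses extra variation and not an empty cell. Covariates chosen from baseline imbalance add parameters to a model that may have only a handful of events behind it.

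At stake is whether the trial can give a usable between-arm estimate and interval for the clinical counterpart of the QT concern. QTc itself is recorded only in a subset of participants, whereas the clinical event is listed without that restriction.

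**Working it through.** **Step 1: exposure, from the plan's own sample size.** Inputs from the Sample size section: "The minimum incidence rate of clinical malaria in SCA patients receiving monthly SP is estimated at 0.2 events per year"; "a hypothesised incidence rate of 0.1 events per person per year in the DP group"; power 0.90; alpha 0.05 (taken as two-sided); 18 months of follow-up; 20% losses.

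- Person-years per arm = (1.960 + 1.282)² × (1/0.2 + 1/0.1) / (ln 2)² = 328.05.
- Divided by 1.5 years, this is 219 per arm, or 438 in total, as stated.
- 438 / 0.8 = 547.5, rounded up to 548, as stated.
- Design exposure is 274 × 1.5 = 411 person-years per arm. This agrees with the stated 9864 person-months: 9864 / 12 / 2 = 411. Counting only the 438 gives 219 × 1.5 = 328.5.

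**Step 2: chance of an empty arm.** The cardiac event rate is an assumption, so a range is shown. With mean count m = rate × 411 in each arm, P(at least one arm empty) = 2e^(−m) − e^(−2m).

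| Assumed rate per person-year, both arms | m | P(at least one empty arm) | P(exactly one empty arm) |
|---|---|---|---|
| 0.001 | 0.41 | 0.89 | 0.45 |
| 0.002 | 0.82 | 0.69 | 0.49 |
| 0.005 | 2.06 | 0.24 | 0.22 |
| 0.01 | 4.11 | 0.03 | 0.03 |
| 0.02 | 8.22 | 0.001 | 0.001 |

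With 328.5 person-years per arm, the second, third and fourth rows become 0.77, 0.35 and 0.07 for at least one empty arm. With a true DP rate ratio of 5 and 411 person-years, the figures for the five SP rates are 0.71, 0.45, 0.13, 0.02 and below 0.001.

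**Step 3: what each method returns for k events against 0, with equal exposure.**

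- Ordinary Poisson: the estimated rate ratio is k/0, so it is infinite (or 0 if the arms are reversed). Software stops at an arbitrary large value. The fits gave log rate ratios of 21 to 22 with standard errors of about 11,900 (k = 5), 18,000 (k = 6) and 15,600 (k = 8), and each was flagged as converged.
- Likelihood-ratio test from the same model: statistic = 2k ln 2.
- Exact conditional test: p = 2 × 0.5^k.
- Firth-penalised Poisson (0.5 added to each count): rate ratio = (k + 0.5)/0.5 = 2k + 1, with a penalised likelihood-ratio p-value.

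| Events | Wald p | Likelihood-ratio p | Exact p | Exact 95% CI | Firth rate ratio | Firth p |
|---|---|---|---|---|---|---|
| 5 v 0 | 0.999 | 0.009 | 0.0625 | 0.92 to ∞ | 11 | 0.027 |
| 6 v 0 | 0.999 | 0.004 | 0.031 | 1.18 to ∞ | 13 | 0.014 |
| 8 v 0 | 0.999 | 0.0009 | 0.008 | 1.71 to ∞ | 17 | 0.003 |

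With no empty arm the methods are much closer. At 5 v 1, the p-values are 0.14 (Wald), 0.09 (likelihood ratio), 0.22 (exact) and 0.12 (Firth).

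**Step 4: operating characteristics, summing over independent Poisson counts at the 5% level.** Under equal rates, the likelihood-ratio test rejects in about 6 to 10% of trials when 1 to 5 events are expected per arm, with a peak of 9.7% at 2. If 1 event is expected on SP and 8 on DP (an assumption, equivalent to 1/411 = 0.0024 per person-year on SP), detection is 27% with Wald, 56% with the exact test, 67% with Firth and 78% with the likelihood-ratio test. The last figure benefits from that test's excess type I error.

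**The case against.** A reader might infer that the plan would report a real cardiac harm as non-significant. That requires a Wald test, and the article names no test or interval type for these models. The likelihood-ratio test from the same Poisson fit stays finite and errs the other way, towards flagging a difference too readily. This part of the objection stands: the text does not support a claim that the error runs in the unsafe direction.

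A reader might also treat this as the trial's central safety outcome. The background names QT prolongation as the main concern. Convulsion or syncope is one of four items in the safety list, under the heading for other outcomes. That objection stands too.

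Rarity is not established. With weekly active or dummy DP doses in both arms, a 48-hour window covers about 2/7 of fully adherent follow-up, and any convulsion in that window counts. Background events could fill both arms, and at 0.01 per person-year or more an empty arm is unlikely. This makes the problem conditional but does not remove it, because the plan has no rule for the case where events are few.

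Events would not vanish from view. Adverse events are to be listed with their relation to the study drug, serious events are reported within seven days, and the DSMB may ask for unblinded data. That limits the harm, but a listing gives no between-arm estimate or interval.

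Finally, the SAP may contain a small-count rule. That would settle the matter if so. But the article does not leave the model for this outcome open: it names it, and it applies the sparse-data argument to a different outcome within the same paragraph.

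**Conclusion.** The point holds as a conditional gap in one secondary safety analysis. The named model gives a rate ratio of 0 or infinity whenever exactly one arm has no serious cardiac events, and the stated fallback does not cure this. How likely that is depends on an event rate the documents do not give: with equal rates and 411 person-years per arm, the chance of at least one empty arm runs from about 0.69 at 0.002 per person-year to about 0.03 at 0.01. In that situation the p-value depends almost entirely on an unspecified choice of test: at 6 v 0 it is 0.999 by Wald and 0.004 by likelihood ratio, with the exact (0.031) and Firth (0.014) values in between. The documents do not support a stronger conclusion that a harm signal would be missed or hidden. The primary analysis is unaffected.

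**What to change.** For serious cardiac adverse events, replace ordinary Poisson regression with one pre-specified sparse-data analysis:

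- report event counts, person-years and rates by arm;
- estimate the rate ratio by Firth-penalised Poisson regression with a profile penalised-likelihood confidence interval, which matches the method already chosen for death;
- adjust for the stratification factors (site and weight band) at most, and not for covariates picked from baseline imbalance;
- give the exact conditional Poisson interval as a supporting figure.

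State in advance that the Firth result is the one to be interpreted, because the two can fall on opposite sides of 0.05 (5 v 0: 0.027 against 0.0625). The cost is a sentence or two of wording and slightly more analysis work. The exact interval is somewhat conservative.

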## Assignment of interventions: allocation

### Sequence generation {16a}

An independent statistician will generate the randomisation sequence in randomly varying block sizes stratified by site and weight band and keep the randomisation code in a locked computer file.

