## Statistical methods

### Statistical methods for primary and secondary outcomes {20a}

#### Analysis populations

Primary analyses will be based on intention-to-treat (ITT) population, and secondary supportive analyses will be done on the per-protocol (PP) population, which is important for cost-effectiveness considerations. Incidence rates will be calculated and rate ratios estimated using Poisson regression, with treatment (as randomised) as the only predictor variable and the stratification factors of site and weight band as co-variates.Intention-to-treat (ITT) population: This population consists of all randomised subjects who have a valid outcomePer-protocol (PP) population: This population is a subset of the ITT population. Subjects with major protocol deviations will be excluded from the PP population. Major protocol deviations will be defined in the SAP

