#### Assessment of efficacy

We will compare incidence rates between intervention groups using incidence rate ratios. Incidence rates will be calculated as the number of events divided by the total follow-up time in each arm. Rate ratios shall be estimated using Poisson regression, with treatment (as randomised) as the only predictor variable and the stratification factors of site and weight band as covariates. In the presence of overdispersion, negative-binomial regression will be used to estimate the incidence rate ratios. Patients who die, withdraw or get lost in follow-up will be censored at their date of death, withdrawal or the last follow-up visit. A *P*-value < 0.05 will be considered statistically significant.

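### Covariates for the secondary count models are chosen from observed baseline imbalance, and the protocol leaves unclear whether site and weight band are in those models

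*Protocol article*

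**What the plan says.** Randomisation uses "randomly varying block sizes stratified by site and weight band" (Protocol article, Sequence generation {16a}). The primary rate-ratio model follows that design. It is a Poisson regression "with treatment (as randomised) as the only predictor variable and the stratification factors of site and weight band as covariates" (Assessment of efficacy), replaced by negative-binomial regression if the counts are overdispersed.

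The section Secondary efficacy outcomes lists six count outcomes: all sick visits, malaria sick visits, all-cause admissions, malaria admissions, serious cardiac adverse events and vaso-occlusive events. They too are analysed by Poisson regression, and "Negative-binomial regression models will be fitted if there is overdispersion". The covariates, however, follow a different rule: "Model adjusters shall be informed by imbalances in baseline characteristics between the intervention groups". The section does not mention site or weight band, does not refer back to the primary model, and names no candidate variables, test or threshold.

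One other place bears on this. Under Analysis populations, within the part headed as covering both primary and secondary outcomes, the Poisson sentence appears again with "the stratification factors of site and weight band as co-variates".

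**The concern.** Adjustment in a randomised trial is justified by prognostic value, not by imbalance. A covariate that happens to differ between arms but does not predict the outcome gains nothing from adjustment; a strong predictor improves precision even when perfectly balanced. The rule therefore uses the wrong criterion. Because it is not specified further, the final model also depends on judgements made once the arms have been compared.

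The factors with the best claim to be in the model are those the trial randomises by, and an imbalance rule is poorly suited to finding them. Site is plausibly prognostic. Study setting {9} describes moderate to intense transmission across the two countries and very high transmission around both Ugandan hospitals. The hospitals range from a 100-bed district hospital to a 1000-bed tertiary centre.

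At stake are the precision of the secondary rate ratios and confidence that their models were fixed in advance.

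**Working it through.** **The plan's own figure.** The point rests on no stated number, but the sample size can be checked to confirm that it is not involved. Inputs from Sample size {14}: rates 0.2 and 0.1 per person-year, power 0.9, level 0.05 (two-sided assumed). Person-years per arm = (1.960 + 1.282)² × (1/0.2 + 1/0.1) / (ln 2)² = 328.05. Total children followed for 1.5 years = 2 × 328.05 / 1.5 = 437.4, rounded up to the stated 438; 438 / 0.8 = 547.5, rounded up to the stated 548. No covariate enters this calculation.

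**How often chance alone produces an imbalance.** For k independent baseline variables screened at 5%, the probability of at least one flag is 1 − 0.95^k:
- k = 8: 0.337
- k = 10: 0.401
- k = 20: 0.642

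Both k and the 5% threshold are assumptions, since the protocol gives neither.

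**Whether the rule would pick site or weight band.** Trials were simulated with 548 children, 1.5 years of follow-up, 4 sites × 4 weight bands, and blocks of 4 or 6 within strata. Site rate multipliers were 2.0, 1.5, 0.5 and 0.3; weight-band multipliers were 1.3, 1.1, 0.9 and 0.7. Eight other covariates were screened at p < 0.05. Apart from the 548 children and 1.5 years, these settings are assumptions. Site was flagged in 0 of 2000 trials and weight band in 0 of 2000. At least one of the eight other covariates was flagged in 33.9%.

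**Cost of leaving them out, by simulation.** Results from 1000 of these trials with no treatment effect, using Poisson models with an estimated scale:

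| Model | Type I error | Mean SE of log rate ratio |
|---|---|---|
| Treatment + site + weight band | 5.2% | 0.158 |
| Treatment + covariates chosen by imbalance | 3.5% | 0.172 |
| Treatment only | 3.4% | 0.172 |

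0.172 / 0.158 = 1.09, so the standard error is about 9% larger than it need be.

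**Cost by formula, across event rates.** With m expected events per child, within-site dispersion 0.5 and between-site squared coefficient of variation 0.3 (both assumed), the variance contribution per child is 1/m + 0.5 with site in the model and 1/m + 0.5 + 0.3 without it. Over 1.5 years:
- 0.1 per year (m = 0.15): √(7.467 / 7.167) = 1.02
- 0.15 per year (m = 0.225): √(5.244 / 4.944) = 1.03
- 1 per year (m = 1.5): √(1.467 / 1.167) = 1.12

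The rate of 0.1 is the protocol's DP rate for the primary outcome, and 0.15 is the mean of 0.1 and 0.2. The rate of 1 per year is an assumption meant for frequent events such as sick visits.

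**Why the simulated 9% exceeds 2 to 3%.** The simulation assumes more heterogeneity. Its site multipliers have mean 1.075 and mean square 6.59 / 4 = 1.6475, so the squared coefficient of variation is 1.6475 / 1.1556 − 1 = 0.43, against 0.3 in the formula. Weight band adds 4.20 / 4 − 1 = 0.05.

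**The case against.** The strongest reply is that the protocol never excludes site and weight band. The sentence under Analysis populations sits within the part covering primary and secondary outcomes, and the secondary count models are Poisson rate-ratio models. It can fairly be read as keeping both factors in every such model, with imbalance-informed covariates as additions. This stands: a reader might infer that the secondary models drop the stratification factors by design, but the text does not say so. The opposite reading is not secure either, because the section specific to secondary outcomes states its own rule and does not refer back. The selection of covariates on imbalance remains under both readings.

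A reader might also infer that primary and secondary rate ratios adjusted for different factors cannot be compared. That does not follow. Suppose each site s contributes the same share w_s of person-time in both arms, and DP multiplies every site rate r_s by a common ratio θ. The unadjusted ratio is then Σ w_s θ r_s / Σ w_s r_s = θ, the same as the adjusted one. Only precision differs.

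Three further points stand in part. The rule looks at baseline data, not outcomes, and the trial statisticians are blinded (Who will be blinded {17a}), which limits selection of a favourable result but does not supply the missing criterion. Study setting {9} says that care guidelines are similar in all four clinics, so the argument that site is prognostic rests on transmission and type of hospital. A statistical analysis plan may well fix a candidate list, but the protocol already fixes the criterion: a plan that followed it would inherit the problem, and one that prespecified covariates would depart from it.

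**Conclusion.** The point holds for the secondary count outcomes. The protocol selects covariates by a criterion that reflects chance and is unrelated to prognostic value, and its text does not settle whether site and weight band are included.

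If they are omitted, the illustrative widening of the standard error is about 2 to 3% at 0.1 to 0.15 events per year and about 12% at 1 event per year, with assumed dispersion 0.5 and between-site squared coefficient of variation 0.3. The simulation gave 9% under stronger assumed heterogeneity. None of these is an estimate for this trial, because the documents give no heterogeneity figures. The 12% should not be taken as the general cost: the rarer outcomes would lose little. The widening arises where overdispersion is modelled, since the variation between sites is then absorbed into the dispersion.

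A reader might infer inflated false positives from leaving out site and weight band. The calculation points the other way (3.5% against 5.2%). What remains is lost precision, conservative tests and analyst discretion; the simulation applied a fixed threshold and does not measure the effect of that discretion. The primary analysis and the sample size are unaffected.

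**What to change.** Replace the sentence on model adjusters with: *All secondary count models include treatment, site and weight band as in the primary model, plus any prognostic baseline covariates named before unblinding; baseline imbalance is described but does not select covariates.* Add that strata will be collapsed for sparse outcomes. Align the Poisson sentence under Analysis populations with this, so that the two sections give the same model.

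The cost is one sentence in the protocol or analysis plan, before unblinding. It needs no new data, since both factors are recorded for randomisation, and it changes no stated figure.

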**Methods:**

This will be a randomised, double-blind, parallel-group superiority trial of weekly single-day courses of DP compared to monthly single-day courses of SP in children with SCA. The study will be conducted in eastern (Uganda) and southern (Malawi) Africa using randomisation stratified by body weight and study centre. Participants will be randomised using an allocation of 1:1 to DP or SP. We will investigate the efficacy, safety, acceptability and uptake and cost-effectiveness of malaria chemoprevention with weekly courses of DP vs monthly SP in 548 to 824 children with SCA followed up for 12–18 months. We will also assess toxicity from cumulative DP dosing and the development of resistance. Participant recruitment commenced on 30 April 2021; follow-up is ongoing.

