## Data collection and management

### Plans for assessment and collection of outcomes {18a}

Before study onset, all the assessors (clinical, nursing, laboratory, pharmacy and data) will undergo study-specific training on study procedures. The internal and external monitors will independently document readiness in the site initiation visits before recruiting the first participant. Twice annual refresher training will be carried out and especially following the subsequent interim monitoring visits.

Following the enrolment visit, participants will return for follow-up at 2 months and then every 2 months thereafter until the required person-months of observation is achieved. The study will refund the costs of transport to the clinic and provide a time compensation. At each visit, all clinical events in the intervening period will be ascertained and those previously not reported or for which the patients did not attend the study clinic will be documented. Participants with < 80% adherence at any one point will have additional counselling.

To determine the outcomes, any participant with a history of fever in the previous 48 h or temperature ≥ 37.5 °C on any visit will have a blood smear for malaria microscopy performed by a certified malaria microscopist. All other SCA-related and non-SCA-related events such as painful crises and hospitalisations will also be documented and reported. In this way, the point prevalence at each visit and the incidence of malaria can be estimated for each study arm without contaminating the intervention in either arm.

The study will provide a standard of care clinical services for sick visits and refer for appropriate care if the level of care required is beyond the capacity of the clinic. All these episodes will be reported as adverse events according to severity. All the adverse events (AEs) and serious adverse events (SAEs) during the intervening period will be documented following ICH GCP principles and all SAEs reported to regulatory bodies, sponsors, DSMB and ethics committees.

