### Methods in analysis to handle protocol non-adherence and any statistical methods to handle missing data {20c}

Primary analyses will be ITT analyses, which will include all participants as randomised regardless of their adherence to the intervention. Every effort will be made to minimise the amount of missing data in the trial, and whenever possible, information on the reason for missing data is obtained. No adjustments will be made for missing outcome data, but missing data may be imputed for covariates.

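### All-cause mortality is compared by a binary logistic odds ratio with no time horizon and no place for censored children, although follow-up varies and 20% loss is planned

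*Protocol article*

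**What the plan says.** All references are to the Protocol article.

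- **Outcome.** Key secondary outcomes lists all-cause mortality, counted from enrolment, with no end point in time.
- **Model.** Secondary efficacy outcomes states "We shall fit a binary logistic model to compare the odds of death between the two intervention groups". Expecting few deaths, it continues: "We shall instead fit models using the firth method, which avoids the convergence challenges of the logistic regression model when the outcome is rare". The effect measure follows: "We shall report odds ratios as measures of association". No time point, offset or time-to-event method is named.
- **Other outcomes.** The same section compares a list of count outcomes, including sick visits and hospitalisations, by incidence rate ratios from Poisson or negative-binomial regression.
- **Censoring.** Under Assessment of efficacy, children who die, withdraw or are lost "will be censored at their date of death, withdrawal or the last follow-up visit".
- **Follow-up.** The abstract speaks of "548 to 824 children with SCA followed up for 12–18 months". Sample size {14} shows that these are two design options: 548 children for an average of 18 months, or 824 for an average of 12. Plans for assessment {18a} sets visits every two months "until the required person-months of observation is achieved".
- **Loss.** Sample size {14} makes one overall allowance of 20% and gives no figure by arm.
- **Analysis set.** Analysis populations restricts intention-to-treat to randomised subjects whose outcome is valid. Section {20c} says these analyses will "include all participants as randomised regardless of their adherence to the intervention", and that missing outcome data will not be adjusted for.

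**The concern.** A binary model needs a yes or no for every child it includes. A child who was alive at the last visit and then lost has neither at the end of the study. Someone must drop that child or class the child as a survivor, and the article gives no rule. The two choices push the odds ratio in opposite directions when loss differs between arms.

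There is also no horizon. Follow-up ends on a trial-wide total of person-months, not at a fixed time per child, so the reported odds describe no defined period.

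The article treats death differently because it will be rare and ordinary logistic regression may not converge. Firth's penalty answers that difficulty. It does nothing for censoring or unequal follow-up. Mortality is a key secondary outcome, and the dates that would solve the problem are already needed for the primary analysis.

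**Working it through.** **1. The plan's own figures.** No figure is given for mortality. The sample-size figures behind the 20% loss do reproduce. With rates of 0.2 and 0.1 per year, 90% power and two-sided 5% (sidedness assumed):

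person-years per arm = (1.960 + 1.282)² × (1/0.2 + 1/0.1) / (ln 2)² = 328.0

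328.0 / 1.5 years × 2 arms = 437.4, so 438. Then 438 / 0.8 = 547.5, so 548, as stated. The 20% is therefore one planning allowance across both arms.

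**2. Set-up for mortality.** The documents give no death rate and no loss by arm, so these are assumptions: a rare, constant death hazard; no true effect; a proportion L of an arm lost evenly over follow-up; loss unrelated to death. Relative to complete follow-up:

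- observed deaths are proportional to person-time, 1 − L/2;
- known survivors are proportional to 1 − L.

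The odds of death are then proportional to (1 − L/2)/(1 − L) if lost children are dropped, and to 1 − L/2 if they are counted as alive. Deaths divided by person-time are unaffected by L.

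**3. Results, DP relative to SP, true ratio 1.00.**

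| Assumed loss, DP / SP | OR, lost dropped | OR, lost counted alive | Rate ratio |
|---|---|---|---|
| 20% / 20% | 1.00 | 1.00 | 1.00 |
| 15% / 25% | (0.925/0.85)/(0.875/0.75) = 0.933 | 0.925/0.875 = 1.057 | 1.00 |
| 10% / 30% | (0.95/0.90)/(0.85/0.70) = 0.869 | 0.95/0.85 = 1.118 | 1.00 |

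Swapping the arms inverts the ratios: 1/0.933 = 1.07 and 1/1.057 = 0.95 for the 10-point difference.

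**4. A second loss pattern.** With exponential death and loss, assumed hazards of 0.01 to 0.05 per year, 1 or 1.5 years of follow-up and the higher loss on DP, results are similar. Loss of 25% / 15% gives about 1.07 (dropped) or 0.94 (counted alive); 30% / 10% gives about 1.14 or 0.88. The rate ratio is 1.00 throughout.

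**5. Equal loss with a real effect.** Under the same exponential model, with 20% loss in both arms and a true hazard ratio of 0.70, the odds ratio is 0.69 to 0.70. What changes is the absolute risk. At an assumed hazard of 0.03 per year, with lost children counted as alive, the SP risk is 2.65% for 12 months of follow-up and 3.95% for 18 months, while the odds ratio stays at about 0.70. The rule for lost children also matters for the reported odds. By the formulas in step 2, each arm's odds are 0.9/0.8 = 1.125 times the complete-follow-up odds if the lost are dropped, and 0.90 times if counted alive, a ratio of 1.125/0.90 = 1.25 between two readings of the same plan.

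**6. Size against sampling error.** Person-time is about 548 × 1.5 × 0.9 = 740 years. Hazards of 0.01 to 0.05 give about 7 to 37 deaths, and a standard error of the log odds ratio of about √(4/D), or 0.76 to 0.33. The shift at 15% / 25% (dropped) is |ln 0.933| = 0.07, about 0.1 to 0.2 standard errors. At 10% / 30% it is |ln 0.869| = 0.14, below half a standard error.

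**The case against.** The strongest reply is that little would change in practice. The trial is 1:1 and double-blind, and each arm takes the other's placebo on the same schedule, so arm-specific loss is less likely than in an open trial. With equal loss unrelated to death, the odds ratio and the rate ratio nearly coincide for a rare event. Deaths will be few, so even the assumed imbalances are small beside sampling error. The tracing described under {18b}, by telephone, sketch map and GPS, may also establish whether some non-attenders are alive. All of this stands and limits the severity.

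It can also be said that the rule for lost children belongs in the analysis plan, which is not shown. That is fair for the rule. It does not cover the choice of a binary model and an odds ratio, which the article states.

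Several stronger readings are tempting but unsupported:

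- **That the odds ratio is biased by differential loss.** No section states or predicts that loss differs by arm. Unequal follow-up alone, if alike in both arms, creates no bias between them.
- **That the two intention-to-treat statements flatly contradict each other.** The sentence in {20c} concerns adherence, and the next remark on missing outcomes is compatible with requiring a valid one. The wording needs aligning, but the conflict is partial.
- **That about 110 children (20% of 548) will be removed.** That is the worst case under a rule the article does not state.
- **That each child is followed for 12 to 18 months.** That range reflects the two design options. Variation between children follows from the stopping rule in {18a}.
- **That death is the only event outcome without a person-time model.** No model is named for parasitaemia or transfusion either.

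**Conclusion.** The point holds in a limited form. The article fixes a mortality analysis whose odds ratio has no stated horizon and which cannot use censored children, when a better method is available from data already collected. Bias between arms is conditional on a difference in loss or follow-up. Under the assumptions in the working, a 10-point difference moves a null odds ratio by about 6 to 7%, and a 20-point difference by about 12 to 14%. The direction depends on an unstated rule. With equal loss there is essentially no distortion of the ratio. The claim that a person-time analysis stays unbiased rests on loss being unrelated to death; if sicker children leave, either analysis is biased. The primary analysis model and the sample size are not affected. Severity is low to moderate.

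**What to change.** Replace the logistic model for death with an analysis of time to death in all randomised children. Death is the event, and other children are censored at withdrawal or last follow-up visit, as under Assessment of efficacy. Firth-penalised Cox regression keeps the protection against sparse events; a person-time rate ratio with an exact or penalised method would also serve. Report a hazard or rate ratio in place of the odds ratio.

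Align the valid-outcome condition under Analysis populations with the as-randomised wording in {20c}, so that each randomised child contributes the person-time observed.

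If the odds ratio is kept, the minimum is to state a fixed horizon and a rule for classing children lost before it.

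The cost is a change of wording and a somewhat less familiar penalised model. No new data are needed. The change does not cure loss that is related to death, so the number lost and the reasons should be reported by arm beside the result.
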